### The current study

The current strategies that are in place to promote healthy movement behaviors of young children in Hong Kong could be enhanced by leveraging the collaborative and complementary roles of parents and educators. In this current study, we aim to enable parents and teachers, so that they may successfully promote healthy movement behaviors in pre-primary school-aged children. The movement guidelines for children aged 2 to 6 years, which have been issued by the CHP will be systematically disseminated to parents and teachers of children enrolled in ECECs in Hong Kong. The dissemination plan will be informed by active engagement with stakeholders through formative work. An evaluation will be conducted to assess the implementation process and the outcomes of the dissemination. Specifically, the evaluation will: (1) assess the uptake of the dissemination of the movement guidelines by parents and teachers of children in ECECs, (2) identify the barriers and enablers to implementation of the movement guidelines in the local context, and (3) evaluate the impact of the school-based dissemination on parents, teachers, and children.

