#### Recruitment

Eight ECECs, from across the three major districts of Hong Kong (i.e., Hong Kong Island, Kowloon, New Territories), will be recruited to join the implementation. The inclusion criteria for ECECs are that they: (1) are included in the published list of kindergartens by the Education Bureau, (2) follow the *Kindergarten Education Curriculum Guide of Hong Kong* [23], and (3) offer classes across three kindergarten levels (i.e., K1, K2, K3). A second group of eight ECECs, who meet the same eligibility criteria and with comparable background to the first group (i.e., ECEC size, location), will also be recruited to join a comparison group for the outcome evaluation. This second group will participate in the activities for the dissemination of the movement guidelines (i.e., educational meetings, social media, resource materials) in the school year following the implementation period. Given the constraints associated with the recruitment of ECECs to participate in projects during a pandemic, the recruitment process will be purposive. The timeline for joining the project will be the prerogative of each ECEC (i.e., hence, the group to which they will be allocated to).

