#### Summative outcome evaluation

A non-randomized observational study design will be used for the outcome evaluation, where outcomes will be compared between the implementation group and the comparison group. The implementation group will consist of teachers and parents from the ECECs that participated in the dissemination activities; the comparison group will consist of teachers and parents from a matched group of ECECs who have yet to join the implementation. ECECs in the comparison group will join educational meetings and receive all materials in the subsequent school year after the implementation period. The primary outcome of interest is the extent to which children in the ECEC groups meet the guidelines for physical activity, sedentary screen time, and sleep. The secondary outcomes are the knowledge and awareness of healthy movement guidelines by teachers and parents.

Teachers and parents will be invited to respond to online surveys at two additional time points: immediately following the implementation period (Time 3, T3), and 4 months post-implementation (Time 4, T4). These surveys will measure the secondary outcome by assessing the participants’ knowledge and awareness of the movement guidelines. The surveys for parents will include additional questions to measure the primary outcome by assessing the extent to which children meet the guidelines through a parent-proxy questionnaire. The said proxy-report questionnaire is made up of items from validated English-language questionnaires [34, 35] which were translated and back-translated [36] for use among parents of young children in Hong Kong. The translated questionnaire had been found to have good internal consistency (Cronbach’s alpha = 0.762), and is currently being used in an ongoing longitudinal study of child development in Hong Kong. Finally, open-ended questions will query on family strategies that relate to children meeting the movement guidelines.

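### Child behaviour is first measured after implementation ends and each ECEC's joining time sets its group, so unmeasured prior differences are mixed into the group odds ratio

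*Protocol article*

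**What the plan says.** All references are to the protocol article.

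- **Aim.** The third aim under *The current study* is to "evaluate the impact of the school-based dissemination on parents, teachers, and children". *Data processing and analysis* describes the logistic regression as determining the contribution of the dissemination activities.
- **Design.** "A non-randomized observational study design will be used for the outcome evaluation, where outcomes will be compared between the implementation group and the comparison group" (*Summative outcome evaluation*).
- **Allocation.** Under *Recruitment*, "the recruitment process will be purposive" and "The timeline for joining the project will be the prerogative of each ECEC (i.e., hence, the group to which they will be allocated to").
- **Comparability.** The comparison group is "A second group of eight ECECs, who meet the same eligibility criteria and with comparable background to the first group (i.e., ECEC size, location"). *Summative outcome evaluation* calls it "a matched group of ECECs who have yet to join the implementation".
- **Measurement.** The outcome surveys take place "at two additional time points: immediately following the implementation period (Time 3, T3), and 4 months post-implementation (Time 4, T4"). Table 3 marks the parent-proxy questionnaire at T3 and T4 and the accelerometer at T3. T1 and T2 fall 3 and 6 months into implementation. Their surveys cover satisfaction, usefulness of materials and knowledge, and Table 3 shows no proxy questionnaire at either.
- **Model.** The terms are group, child characteristics and ECEC, for each guideline component.
- **Limitations.** *Potential challenges and mitigations* acknowledges the lack of randomization. It does not mention that there is no baseline.

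**The concern.** When groups form by self-selection, the usual protection is to measure the outcome before exposure, so that the analysis can adjust for it or compare changes. Here no such measurement exists in either group. A T3 difference in the proportion meeting a guideline could come from the dissemination, from behaviour that already differed in September 2021, or from whatever made some ECECs ready to join a year sooner. The model cannot tell these apart.

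At stake is the third aim. The bias does not shrink with sample size, and a later analysis plan cannot adjust for a baseline that was never collected. The measurement schedule and the allocation rule are both fixed in the article, so this is not a detail left to another document.

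**Working it through.** **1. Is there any usable baseline?** T1 and T2 are during implementation and do not measure child behaviour. The formative focus groups (six ECECs, 18 teachers and 18 parents) were qualitative, and the article reports no measurement of children from them. The first child measurement is therefore at T3.

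**2. Does the ECEC term help?** Each of the 16 ECECs lies wholly in one group. As fixed effects, the ECEC indicators determine group exactly (group is the sum of eight of them), so a separate group effect cannot be estimated. As random effects, they correct the precision of the group coefficient but leave this bias in place.

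**3. How large a prior gap matters?** Inputs from the plan: design OR 1.5 and 240 expected complete responses (*Participants and sample size*). Assumptions: 120 per group, zero true effect, and a comparison rate of 30%. *Background* reports under 30% for 180 minutes of daily activity; the sample-size text states no rate.

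Apparent OR = [p1/(1 − p1)] / [p0/(1 − p0)], with p1 the implementation-group rate before dissemination.

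- 5-point gap: (0.35/0.65)/(0.30/0.70) = 1.26
- 10-point gap: (0.40/0.60)/(0.30/0.70) = 1.56

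The gap that alone equals the design OR comes from p1 = 1.5·p0/(1 − p0 + 1.5·p0):

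| Assumed p0 | p1 | Gap (points) |
|---|---|---|
| 20% | 27.3% | 7.3 |
| 30% | 39.1% | 9.1 |
| 50% | 60.0% | 10.0 |

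**4. The other direction.** If the implementation ECECs began 5 points lower, the prior OR is (0.25/0.75)/(0.30/0.70) = 0.78. A true OR of 1.5 would then appear as 0.78 × 1.5 = 1.17, if the effect multiplies the odds. A starting rate of 22.2% (prior odds 0.429/1.5 = 0.286) would hide it completely.

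**5. How often would a prior gap give p < 0.05?** Two-sided two-proportion test, 120 per group, no clustering or covariates. With d the gap, s0 the pooled and s1 the unpooled standard error, P = 1 − Φ[(1.96·s0 − d)/s1] + Φ[(−1.96·s0 − d)/s1]. At d = 0.10, s0 = √(2 × 0.35 × 0.65/120) = 0.0616 and s1 = √((0.24 + 0.21)/120) = 0.0612, giving 37%. At 8 points the result is 26%, and at 5 points 13%.

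**6. Chance imbalance alone.** The SD of the gap between two sets of eight ECECs is √(ICC × 0.30 × 0.70) × √(2/8). An assumed ICC of 0.01 gives 2.3 points and 0.10 gives 7.2 points, before any self-selection.

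The planned total of 242 does not enter these steps. It is not reproduced for a binary group predictor (850 two-sided at a 30% comparison rate), but that is a separate matter and lends no support here.

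**The case against.** The plan is open about its design. It calls the study non-randomized, gives pandemic recruitment as the reason, and lists the lack of randomization as a limitation. It also has real safeguards. Both groups must be on the Education Bureau list, follow the same curriculum guide and offer all three kindergarten levels; size and location are to be comparable; and the model adjusts for child characteristics. A condensed article need not list every covariate.

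Much of this stands, and it rules out several stronger readings that a reader might infer:

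- *Every prior difference is counted as effect.* No. Differences explained by eligibility, size, location or measured child characteristics are at least partly removed.
- *The process evaluation is the only remedy offered.* No. The safeguards above are remedies too, though incomplete. The process evaluation itself draws on the implementation group only and cannot show how the groups differed beforehand.
- *The bias favours the dissemination.* The documents do not show this. ECECs with low activity might join early as readily as active ones.
- *The groups are known to differ.* Nothing in the article shows that they do. The gaps above are assumptions.
- *The omission of family factors is an error in itself.* The exact covariate list may be elsewhere. The article names parents' long working hours as a hindrance and lists care by grandparents and nannies as a local practice to be addressed. That makes both sensible candidates, not proven confounders.

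What the objection does not answer is the absence of any prior measurement of child behaviour, together with a causal aim and no statement of that gap among the limitations.

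**Conclusion.** The point holds in this limited form. The T3 and T4 group odds ratios combine the effect of dissemination with prior differences that shared eligibility, size, location and child characteristics do not capture, notably prior child behaviour and motivation to join early. The direction is unknown. Gaps of about 7 to 10 points at comparison rates of 20% to 50% would by themselves equal the effect the study is sized to detect; a 5-point gap at 30% would give about half of it on the log-odds scale (ln 1.26/ln 1.5 = 0.57). These sizes rest on assumed rates and gaps and on unadjusted arithmetic. The schedule and the allocation rule do not depend on those assumptions. As planned, the comparison supports a statement of association, not of impact.

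**What to change.** 1. **Baseline where still possible.** In any ECEC where dissemination has not begun, give the existing online parent-proxy and knowledge questionnaire before the first educational meeting. Where both groups have it, adjust the T3 model for each child's baseline status. *Status and timeline of the study* puts the start at September 2021, and the first face-to-face sessions were due in the first month, so this is probably too late for the implementation group. A baseline in one group only cannot adjust the comparison.
2. **Otherwise, measure and adjust.** Add parental working hours and main caregiver to the T3 parent survey, record ECEC size and district, and enter all four in the model. ECEC itself should enter as a random effect or through clustered standard errors, so that the group coefficient can be estimated.
3. **Wording where both groups lack a baseline.** Report the T3/T4 comparison as an association instead of *impact* or *contribution*, state the missing baseline as a limitation, and replace *matched* with *comparable in size and location*.
4. **Optional supplement.** Repeat the survey at the end of the comparison ECECs' own dissemination year, with their T3 as the pre-exposure measurement. This before-after estimate carries age, cohort and secular-trend bias and needs follow-up beyond the last planned contact in September 2022, so it cannot replace the steps above.

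The cost of steps 1 to 3 is a few survey items or one extra online round, some burden on parents, and a weaker stated conclusion. Step 2 reduces confounding by the named factors only; prior behaviour and motivation would remain.

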For a further measure of the primary outcome, parents will also be invited to let their children wear accelerometers for objective measurement of physical activity, sedentary behavior, and sleep. The Actigraph GT3X (Actigraph, Pensacola, FL, USA) will be used, which is an accelerometer equipped with antero-posterior, vertical, and medio-lateral axes [37]. The GT3X is a widely used device for physical activity and sedentary behavior monitoring, and cut-points have been validated for young children [38]. Evidence-based accelerometer data collection for children will be followed [39]. Accelerometer epoch length will be set at 15 s, and each child will be asked to wear the GT3X above the right hip on a waist belt during waking hours for seven consecutive days. The parents/caregivers will also be instructed to remove the GT3X during water-based activities (e.g., bathing, swimming), and to record the time when the GT3X was put on and removed (i.e., record the wear/non-wear time in a diary).

The data gathering procedures for the process and outcome evaluations are summarized in Table 3, according to the timeline of measurements.

**Table 3 Tab3:** Timeline of data gathering procedures for the process and outcome evaluations

	Time 1	Time 2	Time 3	Time 4
Participation audit	•	•		
Online metrics	•	•		
Online survey (knowledge and awareness of movement guidelines)	•	•	•	•
Focus group discussions	•	•		
Online survey (parent-proxy questionnaire on primary outcome)			•	•
Accelerometer monitoring			•	

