#### Data processing and analysis

For the process evaluation, quantitative data obtained from the participation audit, online metrics, and online survey (close-ended questions) will be analyzed using descriptive statistics, and explored using cross-tabulations to identify differences (if any) between participant groups (i.e., teachers/administrators, parents/caregivers) and between ECECs. Qualitative data obtained from the online survey and outcomes questionnaire (open-ended questions), and transcribed FGDs will be examined using thematic analysis, guided by a realist framework which assumes that language captures participants’ experiences of reality [40]. A six-phase analytic process will be adopted consisting of: familiarizing with the data, generating codes, generating initial themes, reviewing and developing themes, refining, defining, and naming themes, and writing the report [22]. Coding and theme generation will take inductive (i.e., bottom up approach) and semantic approaches (i.e., explicit meaning of gathered data) as these are known to align well with a realist framework [40]. Thematic analysis will be supported by NVivo 12.0.

Findings from the quantitative and qualitative analyses will be converged, guided by the RE-AIM framework [25] to answer the evaluation questions (see Table 1). The converged analysis will account for participant groups and individual ECECs, accounting for differences in the background and volume of engagement during the implementation.

For the outcome evaluation, the proportions of children who meet the guidelines will be measured based on the parent-proxy questionnaire and accelerometer monitoring. A minimum of 4 days of accelerometer data will be required to be considered valid [39]; cut-points developed by Evenson et al. [41] and Pate et al. [42] have been recommended to determine time spent in physical activity and sedentary behavior in young children [37]. Meeting the guidelines is defined as ≥180 min/day of total physical activity (of which 60 min is vigorous physical activity), ≤1 h/day of sedentary screen time, and 10–13 h of sleep per 24-h period [4]. Logistic regression will be conducted to determine the contribution of the dissemination activities (i.e., implementation or comparison group), child characteristics, and ECEC on the likelihood of a child meeting each guideline component (i.e., primary outcome).

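### The accelerometer is named as an objective measure of sleep but is worn only in waking hours, so the sleep component rests on parent report alone

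*Protocol article*

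**What the plan says.** All references are to the protocol article.

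- **Purpose of the device** (Summative outcome evaluation). The accelerometer is introduced with the words "For a further measure of the primary outcome", and "parents will also be invited to let their children wear accelerometers for objective measurement of physical activity, sedentary behavior, and sleep".
- **Wear schedule** (same paragraph). "each child will be asked to wear the GT3X above the right hip on a waist belt during waking hours for seven consecutive days". Parents also take it off for water-based activities and are asked "to record the time when the GT3X was put on and removed".
- **Timing** (Table 3). Accelerometer monitoring is marked at T3 only. The parent-proxy questionnaire on the primary outcome is marked at T3 and T4.
- **Use in the analysis** (Data processing and analysis). "the proportions of children who meet the guidelines will be measured based on the parent-proxy questionnaire and accelerometer monitoring". The sentence does not assign a source to each component.
- **Thresholds** (same section). Besides the physical activity criterion, these are "≤1 h/day of sedentary screen time, and 10–13 h of sleep per 24-h period".
- **Processing** (same section). At least 4 days of data are needed for validity, and the published cut-points are used "to determine time spent in physical activity and sedentary behavior in young children". Sleep is not among their outputs.
- **Rationale** (Potential challenges and mitigations). Objective and subjective measures each have weaknesses, and using both is meant to compensate.

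**The concern.** The stated purpose and the wear instruction stand in the same paragraph and cannot both be carried out. This is a conflict between two things the article says, not a detail left to a fuller document.

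The objective check matters because the alternative source is parent report in a non-randomized comparison. Parents in the implementation group will have been taught the specifications and benefits of the guidelines before they report whether their child meets them; parents in the comparison group will not yet have been. Reports could therefore differ between groups without any difference in the children's sleep. The article does not quantify such a shift, and neither can this review, but it is the kind of error a device measure would help to detect. Each guideline component is analysed separately, so the sleep comparison would stand without that check while the article tells readers that it has one.

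Timing adds to this. There is a single device wave, so sleep not recorded at T3 cannot be recovered later.

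**Working it through.** The plan gives no figure on this point to reproduce. The sample size is set on parent responses and does not depend on the device. The check sets the stated purpose, the wear schedule and the thresholds side by side.

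**1. Hours of sleep recorded.** Inputs: a sleep threshold of 10 to 13 h per 24 h, and wear in waking hours only.

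- Waking time for a child within the sleep range = 24 − sleep: 24 − 13 = 11 h and 24 − 10 = 14 h.
- Maximum recording time under the instruction is therefore 11 to 14 h per day, less water activities.
- Sleep recorded = sleep time falling within wear time = 0 h. The device is off for the whole of the 10 to 13 h to be classified.

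**2. Can the on/off diary stand in?** For a given day, diary off-time = sleep + water activities + any time the device is off while the child is awake. Call the last two terms together x, with x ≥ 0. Then:

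- off-time = sleep + x, so off-time is an upper bound on sleep, provided the device is never worn during sleep;
- a child who sleeps 10 − x hours would show 10 h off and be counted as meeting the lower limit, and a child who sleeps more than 13 − x but no more than 13 h would show more than 13 h off and be counted as exceeding the upper limit.

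The article gives no value for x. Whatever its size, the diary is kept by the parent, so it is not an objective source. At best it is a rough proxy for time in bed.

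**3. Does the processing offer another route to sleep?** No. The named cut-points return time in physical activity and in sedentary behavior. The validity rule counts days and says nothing about nights, which fits a waking-wear protocol.

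**4. Source by component, as written.**

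| Component | Parent questionnaire (T3, T4) | Accelerometer (T3) |
|---|---|---|
| Physical activity | yes | yes |
| Sedentary screen time | yes | total sedentary time only; the article does not claim screen time |
| Sleep | yes | claimed, but not recorded |

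The contradiction lies in the last row. The middle row is a point of wording: sedentary time from an accelerometer does not show whether a screen was in use, so the limit of 1 h per day cannot be applied to it.

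**The case against.** The strongest reply is that little depends on the device. It is a further measure, children are invited rather than required to wear it, it is used once, and the questionnaire addresses all three components at both outcome time points. The analysis sentence names the two sources jointly and can be read as complementary use: the device for activity, the questionnaire for the rest. A condensed article may also leave sleep scoring to a fuller document.

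Much of this stands, and it limits the point. Three stronger readings that a reader might infer are not supported:

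- **That two of the three components fail on the device in the same way.** Nowhere does the article say that the accelerometer measures screen time. It says sedentary behavior, which the device and its cut-points do address. Only sleep is both promised and ruled out.
- **That an analyst would be forced to count non-wear as sleep, or sedentary time as screen time.** No such rule is stated, and the questionnaire is available for both components.
- **That the primary outcome cannot be measured.** It can, by parent report, for every component.

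What the reply does not remove is the conflict itself. Sleep is named expressly among the objective measurements, and the wear instruction excludes it. An unstated scoring method alone would be no finding; a stated schedule under which there is nothing to score is one.

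**Conclusion.** The point holds for sleep. As written, the accelerometer gives 0 h of sleep data, so the sleep component rests on parent report alone at both T3 and T4. The stated benefit of pairing an objective with a subjective measure does not apply to it. The loss is one objective cross-check, on one of three components, at one time point. It changes how firmly a group difference in sleep can be interpreted, but not whether the primary outcome can be analysed.

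The conclusion assumes that families follow the wear instruction as printed. If some children slept in the device, the resulting data would be unplanned and selective and would not restore the measure. For screen time the article contains no error, only an unassigned data source that should be spelled out.

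**What to change.** Reconcile the two statements before the T3 accelerometer wave, in one of two ways.

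1. **Keep sleep as a device outcome.** Change the instruction to 24-hour wear with removal only for water-based activities. Add bed, wake and nap times to the diary already issued; naps matter because the threshold is per 24 h. Name a sleep-scoring method and a valid-night rule beside the existing 4-day rule. The cost is a revised parent instruction, extra diary entries, additional processing, and possibly lower overnight compliance, for which the article gives no estimate.
2. **Drop sleep from the device outcomes.** Delete it from the sentence on objective measurement, state that sleep is parent-reported only, and limit the statement about the two methods compensating for each other accordingly. This costs wording only. It is also the only option left if the T3 wave has already been run with waking-hours wear.

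Under either option, add a short statement of source by component to Data processing and analysis: screen time from the parent questionnaire only; physical activity from the questionnaire and the accelerometer; sleep from the questionnaire, plus the accelerometer only if option 1 is taken.
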